### Cost analysis

The cost analysis will report the resource use and cost of the intervention. For the intervention and control group, survey and registry-based data on resource use, including services provided in the health care sector (primary and secondary care) and pharmaceuticals, will be aggregated for each individual in intervals determined by the time of data collection. Cost data will be interpolated to total cost for the whole observation period (18 months). The aggregated cost data will be analyzed as costs attributable to the intervention (that is difference in difference) and reported as mean values with 95% (bootstrap) CIs. Due to the non-normal distribution of cost data generalized linear models will be employed with appropriate choice of link function.

The analysis of cost-effectiveness will compare the observed gain in Quality-Adjusted Life Years (QALYs) (HR-QoL over 18 months) with the observed incremental cost (over 18 months) by estimating incremental cost-effectiveness ratios (ICER). To express statistical uncertainty in the ICER estimates acceptability curves will be developed to express the likelihood of the intervention being cost-effective at various QALY threshold values.

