#### Cost data

For the analysis of intervention costs, activities related to the intervention will be registered for each individual patient by the health care providers. In addition, data will be collected on time use related to each activity and relevant unit cost of resources. Other resource use and costs related to health care provisions will be obtained for each patient from the national health registries for hospitals, primary care, and purchase of prescription medication will be obtained from primary care pharmacies. These data will be obtained from the National Board of Health. Due to the confidentiality of these data (prescription data) they will be stored and analyzed through Statistics Denmark’s Research computer.

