### Statistical analysis

The scoring of the standardized questionnaires will be carried out according to the guidelines from instrument developers. All data analyses will be carried out according to a pre-established analysis plan; all analyses will be done applying SAS software (v. 9.3; SAS Institute Inc., Cary, NC, USA). All descriptive statistics and tests will be reported in accordance with the recommendations of the ‘Enhancing the QUAlity and Transparency Of health Research’ (EQUATOR) network: the CONSORT statement [55]. In order to evaluate the empirical distributions of the continuous outcomes, visual inspection will be used to suggest whether the assumption of normality is reasonable. The univariate procedure (PROC UNIVARIATE) statement will be used for summarizing the data. All analyses will be conducted according to the ITT principle; that is analyzing participant outcomes according to the group to which they are randomized, even if some participants do not receive the intervention according to the randomization. We will run the analyses where missing data are imputed by multiple imputation. For sensitivity we will also perform analyses ‘as observed’ analyses where we will not use any missing data imputation. All reported *P*-values and 95% confidence intervals (95% CI) will be 2-sided and will not be adjusted for multiple comparisons. Unless stated otherwise, results will be expressed as the difference between the group means and 95% CI with the associated *P*-values, based on a general linear model (GLM). Data will be analyzed using a one-factor ‘Analysis of Covariance’ (ANCOVA), with a factor for Group, using the baseline value as covariate to reduce the random variation and increase the statistical power.

Proportions will be compared by estimating the risk difference with 95% CIs for each dichotomous outcome; including a Wald-Z-test for the null hypothesis that there is no difference between the proportions.

Secondly, to relate the results to compliance, a ‘per protocol’ analysis will also be used. The ‘per protocol’ population is defined as the patients who have ‘completed’ the intervention to which they were allocated according to the principles described in the intervention section above.

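### Costs are to be analysed as a difference in difference, which under randomization is unbiased but in large samples never more precise than using baseline cost as a covariate

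*Protocol article*

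**What the plan says.** The Cost analysis section names its between-arm contrast: "The aggregated cost data will be analyzed as costs attributable to the intervention (that is difference in difference". Results are to be mean values with bootstrap confidence intervals. The model is given only in outline: "Due to the non-normal distribution of cost data generalized linear models will be employed with appropriate choice of link function". No model terms, link or baseline cost window are stated.

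For outcomes in general, the Statistical analysis section plans an ANCOVA with group as the factor, "using the baseline value as covariate to reduce the random variation and increase the statistical power". That default is introduced with a proviso: "Unless stated otherwise, results will be expressed as the difference between the group means and 95% CI".

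For cost-effectiveness, the QALY gain is to be set against the "observed incremental cost (over 18 months) by estimating incremental cost-effectiveness ratios (ICER"), and "To express statistical uncertainty in the ICER estimates acceptability curves will be developed".

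On data sources, the Cost data section says: "Other resource use and costs related to health care provisions will be obtained for each patient from the national health registries". The Cost analysis section also mentions survey data, and adds: "Cost data will be interpolated to total cost for the whole observation period", which it gives as 18 months.

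**The concern.** Difference in difference earns its place where groups differ systematically before treatment. Here allocation is 1:1 at random, so expected pre-trial costs are equal in the two arms and there is no bias to remove. Subtracting each patient's own baseline cost fixes the slope on baseline at 1, whether or not the data support that slope, and so carries baseline noise into the estimate. A covariate lets the data choose the slope. The article gives precision as its reason for covariate adjustment of the other outcomes, and gives no reason for treating costs differently.

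At stake is the precision of the incremental cost with 150 patients. Cost-effectiveness is one of the stated secondary objectives, and the incremental cost is one of the two inputs to an ICER.

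**Working it through.** **Plan's own figures.** The article gives no figure for the precision of costs or the ICER. Its only such figures concern sitting time (50 minutes, SD 102, two-sided 0.05). They reproduce with the exact two-sample t-test: 80.4% power at 67 per group and 84.7% at 75. Nothing below touches them.

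**Inputs.** From the article: 1:1 allocation, 75 per group, difference in difference for costs. Assumed, because the article does not give them: r, the correlation of a patient's baseline and follow-up cost; σb and σf, the cost SDs at baseline and follow-up.

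**Formulas** (large samples, linear contrast, variance per patient within an arm):

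- Difference in difference: σf² + σb² − 2rσbσf, which is 2(1 − r)σ² with equal SDs.
- Baseline as covariate: σf²(1 − r²).
- First minus second: (σb − rσf)², which is never negative. The two methods tie only when σb = rσf.
- With equal SDs the variance ratio is 2(1 − r)/(1 − r²) = 2/(1 + r), so the SE ratio is √(2/(1 + r)). The equivalent number of patients is 150(1 + r)/2.

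**Equal SDs:**

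| Assumed r | Variance, difference in difference (σ² = 1) | Variance, covariate | SE ratio | 150 patients count as about |
|---|---|---|---|---|
| 0.3 | 1.40 | 0.91 | 1.24 | 98 |
| 0.5 | 1.00 | 0.75 | 1.15 | 112 |
| 0.7 | 0.60 | 0.51 | 1.08 | 127 |
| 0.8 | 0.40 | 0.36 | 1.05 | 135 |

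The last column applies to the cost contrast only. Comparing follow-up costs with no baseline adjustment has variance 1.00 on this scale. Below r = 0.5, difference in difference is therefore worse even than ignoring baseline: √1.40 = 1.18 at r = 0.3.

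**Unequal SDs.** The SE ratio is √[(1 + k² − 2rk)/(1 − r²)] with k = σb/σf. At k = 0.5 and r = 0.5 it is √(0.75/0.75) = 1.00, so the loss vanishes. At k = 1.5 it is 1.50 to 1.61 for r from 0.3 to 0.8.

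**Skewed costs.** A simulation with lognormal costs (log-scale SD 1), 75 per arm and 4,000 runs gave SE ratios of 1.27, 1.18, 1.13 and 1.13 at r = 0.3, 0.5, 0.7 and 0.8. Bias was negligible for both methods.

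**Carry-over to the ICER, if this estimate is used there.** Let s be the cost share of the net-benefit variance under covariate adjustment, ignoring cost–QALY covariance. The SE of net benefit is then multiplied by √[1 − s + 2s/(1 + r)]:

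| s | r = 0.3 | r = 0.8 |
|---|---|---|
| 0.25 | 1.065 | 1.014 |
| 0.75 | 1.185 | 1.041 |

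That is roughly 1% to 19%.

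**The case against.** The strongest reply is that this is a preference about efficiency and not an error. Difference in difference is valid under randomization, the article claims no power or precision for costs, and the ANCOVA default expressly yields where something else is stated, so the two sections do not contradict each other. All of that stands. It limits the weight of the point but does not make the named contrast the better choice.

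A second reply is that the planned generalized linear model has no listed terms, so a baseline cost covariate is not ruled out and may appear in the separate analysis plan. That is fair for details left open. The contrast itself is not left open: the article names it.

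A third reply is that the size rests on undocumented inputs. It does, which is why a range is shown, including r = 0.8 and unequal SDs. With a non-identity link the linear formulas hold only approximately.

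Three stronger readings go further than the text allows:

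- **That the ICER's uncertainty is certainly widened.** The article feeds the ICER with an observed incremental cost and does not say that this is the difference-in-difference estimate.
- **That the cost result would be a ratio of ratios, unusable in an ICER.** This depends on a link not yet chosen, and the article promises mean values.
- **That interpolation is wrong throughout.** Survey data are also used and may need it. The point holds only for dated registry costs that already cover the period.

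**Conclusion.** The point holds as a matter of efficiency. For the linear contrast in large samples, difference in difference can at best equal baseline-as-covariate. With equal SDs, the SE of the cost difference is about 5% to 24% larger for assumed r from 0.8 down to 0.3. The loss can disappear when baseline costs vary less than follow-up costs, and it exceeds this range when they vary more. Any effect on the ICER is conditional on this estimate being used there. It is then roughly 1% to 19% in the SE of net benefit, for cost shares of 25% to 75% of the variance.

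A reader might infer that the incremental cost would be biased, or that the trial's main result is in doubt. Neither follows: randomization protects both estimators from bias, and the primary outcome and sample size are not involved.

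**What to change.** In the Cost analysis section, replace the parenthesis that names difference in difference with the following:

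- Fit a generalized linear model to each patient's total cost over the same period as the QALYs. Use arm as factor and pre-baseline cost as covariate, taking the same baseline cost that difference in difference would need.
- Report the incremental cost as the averaged predicted difference between arms on the cost scale, with a bootstrap CI.
- State that this estimate enters the ICER and the acceptability curve.
- Sum dated registry costs directly where they cover the period, and limit interpolation to survey-based items.

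Keep the cost and QALY periods identical. The article sets both at 18 months, whereas Participant timeline puts the whole trial at 22 months. Extending only the costs to the last follow-up would mismatch the two parts of the ICER.

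The cost is a change of analysis wording. There are no added visits or patient burden, and no baseline cost data are needed beyond what difference in difference already requires.

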## Monitoring

### Ethics, confidentiality and dissemination

The trial will be performed in accordance with the Helsinki Declaration. The project has been approved by the Regional Committee on Biomedical Research Ethics September 2012 as registry-based research (REC; reference number, H-2-2012-112, document number, 37276). The study was approved by the Danish Data Protection Agency (ref number 711-1-08). All formal and safety rules in the process from data collected for publication are observed (Danish Data Protection Agency, Research Ethics Committee, Clinicaltrial.gov, information technology (IT) issues, and so on). Anyone who has access to the full relevant data sets (chief executive, all supervisors, and project staff) is familiar with the formal and safety rules. All information collected during the course of the study will be kept strictly confidential in accordance with Danish Data Protection Agency rules; operationally, this will include consent from the patients.

It is planned to publish at least four scientific papers based on the trial in peer-reviewed journals.

In addition, the following sources are included in the communication plan:Papers (peer-reviewed and popular science)Presentations at conferences (national and international) or similarCollaboration with the Danish Rheumatism Association - both members and groups of employeesOther relevant patient organizations covering patients with musculoskeletal diseases, and press

### Access to data

RC will analyze data in collaboration with TT, [name], MA. JS will analyze the cost-effectiveness data. The project group will have access to data as well as to the DANBIO registry [37,56]. The patient data in DANBIO are protected by a unique log-in for each user. Data are encrypted and logged. Data generated in the trial belong to Glostrup Hospital, University of Copenhagen. The steering group ‘Joint Resources’ will be involved in the case of query about access to data.

## Discussion

This trial protocol describes the design of an innovative randomized controlled trial, which aims to test whether sedentary behavior can be reduced in patients with RA through behavioral lifestyle change. To the best of our knowledge, this is the first randomized trial to investigate the effect of an individually tailored motivational counseling intervention on daily sitting time in patients with RA. The intervention is developed and based upon results from studies in population-based samples of sedentary adults and in elderly and obese sedentary populations. The population under study, men and women with RA, represents a group of patients with chronic disease and increased risk of developing diabetes and cardiovascular diseases. In addition, a large proportion of patients with RA struggle with strained joints and immobility in daily life. If effective, the intervention may reduce the risk of cardiovascular disease and type 2 diabetes in patients with RA by reducing their daily sitting time. It should be noted that a possible reduction in sitting time, the primary outcome, does not necessarily imply a reduction in cardiovascular disease (CVD) risk. However, a possible effect of the intervention on secondary outcomes, CVD biomarkers (cholesterol and so on) will be simultaneously registered and studied.

We cannot rule out that wearing an ActivPAL® may cause reactivity and as such in itself act as a ‘behavioral intervention’. However, participants in both groups are measured at baseline and follow-up, and the size of the between arm difference is, therefore, not likely to be affected or considered in the sample size calculation. Also ActivPAL® monitors start measuring from midnight following the first day of application in order to minimize reactivity by allowing participants to get used to wearing the device. Finally, the ActivPAL® measurements are not shown to participants until after the study is completed.

It should be noted that in behavioral intervention RCTs patients are difficult to blind. We could have offered the control group participants a ‘sham’ counseling intervention with counseling on something else than reduction of sedentary behavior. However, this could potentially induce an effect in the control group which we wanted to avoid.

We expect the intervention to result in reduced pain (less use of painkillers), reduced fatigue, increased daily physical functioning, improved self-efficacy and better general health status. The intervention is simple and could relatively easily be implemented in clinical practice along with lifestyle advice and recommendations on physical activity, sports and exercise, diet and smoking habits. In addition, we expect the intervention method to be transferable to other groups of chronically ill individuals with prolonged sitting time and mobility limitations.

## Trial status

Recruitment for the trial is planned to start in April 2013 and will end in December 2014.

## Abbreviations

ACPA: anti-citrullinated protein antibody
ACR: American College of Rheumatology
ANCOVA: Analysis of Covariance
BMI: body mass index
COPD: chronic obstructive pulmonary disease
CRP: C-reactive protein
CVD: cardiovascular disease
DANBIO: Danish National Board of Health biological therapies database
DAS 28: Disease Activity Score Based on 28 Joints
EQUATOR: Enhancing the QUAlity and Transparency Of health Research
EQ-5D-5 L: EuroQol
GLM: general linear model
GSES: The General Self-Efficacy Scale
HAQ: Health assessment questionnaire
HbA1c: glycosylated hemoglobin, type A1c
HR-QoL: health-related quality of life
ICER: incremental cost-effectiveness ratios
IgM-RF: rheumatoid factor of the immunoglobulin M class
IPAQ: International Physical Activity Questionnaire
IT: information technology
ITT: intention-to-treat
LDL: low-density lipoprotein cholesterol
METs: Metabolic Equivalent of Task
MFI: Multi-dimensional Fatigue Inventory
MI: motivational interviewing
MOSPAQ: Medical Outcomes Study Patient Assessment Questionnaire
MVPA: moderate and vigorous physical activity
OPAQ: Occupational Physical Activity Questionnaire
PAS: Physical Activity Scale
PROC UNIVARIATE: univariate procedure
QALYs: Quality-Adjusted Life Years
RA: rheumatoid arthritis
SF-36: The Short Form Health Survey
SMS: Short Text Message Service
VAS: The Visual Analogue Scale
VLDL: very low-density lipoprotein cholesterol
